## Methods/design

### Study design

In this multisite randomized controlled trial, we will evaluate the effects of the START intervention on ART adherence and HIV virologic suppression. We will recruit 240 patients with HIV at two HIV clinics, with each randomized to receive either START or usual care at a 1:1 ratio at each clinic (60 patients in each arm at each site). Random assignment codes will be computer-generated and placed in a sequential list that will be maintained by the principal investigator. Assignments will be issued to study coordinators once candidates have enrolled and completed the baseline survey. The randomization will be stratified by prior ART history (naïve or experienced) and CD4 count (<350 vs. ≥350 cells/mm^3^) because of the influence that prior ART history may have on adherence and clinical outcomes, and also due to our interest in determining whether early-stage patients can adhere as well as other patients to treatment. There is no way to blind the participants to whether they are receiving the intervention; this could potentially influence adherence performance and retention, as clients may feel more or less incentive to perform well in light of whether they receive the intervention. We do not see a way to prevent this potential bias, nor do we have a way to distinguish such effects from actual intervention effects; however, this limitation will be cited in reports of study findings.

Primary outcomes will be optimal dose-taking adherence (>85 % prescribed doses taken), as measured with electronic monitoring caps, and undetectable HIV viral load. Secondary outcomes will include dose-timing adherence (>85 % prescribed doses taken on time) and CD4 count. Primary endpoints will be month 6 (short-term effect) and month 24 (to test durability of effect), though electronic monitoring will be continuous and a fully battery of assessments will be administered every 6 months for 24 months. See Fig. 1 for the flow of participant procedures through the protocol. Participants will be paid $30 for each completed assessment, as well as a $50 bonus if they complete all five primary assessments and $10 for each attended intervention session. To limit attrition, contact information will be collected at enrollment and verified at each follow-up visit. Furthermore, the study coordinator will check with all study participants at the midway point between surveys, which will be timed to coincide with regular scheduled clinic appointments.

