### Study sample

Eligibility criteria include (1) patient and provider plan to start or restart (not currently on ART) the patient on ART; (2) patient has stable health status and no acute opportunistic infections or medical conditions (including acute HIV infection) that warrant starting ART immediately, as determined by the patient’s provider; (3) detectable HIV viral load at last test (within past 6 months); (4) if CD4 count is <200 cells/mm^3^, patient is on prophylactic medication to limit risks associated with the intervention’s imposed delay in starting ART; (5) patient is age 18 years or older; and (6) patient speaks English. Providers will inform eligible patients of the study, and patients who interested in participating will be referred to the study coordinator for consent procedures, eligibility screening, baseline survey, and randomization. Written informed consent will be obtained from all participants at enrollment. For control patients, the baseline visit is scheduled for the same day or within 1 week of the screening assessment. The baseline visit for intervention patients will take place on the same day as the last pretreatment intervention session (once they achieve >85 % dose-taking adherence during a practice trial).

We calculated the size of effects that this sample can detect with 80 % power (two-tailed test) with regard to the primary outcomes. On the basis of the pilot study [14], we expect that 40 % of the control group will achieve optimal (>85 %) dose-taking adherence and 45 % will achieve undetectable viral load. With these expected rates in the control group, together with estimates of 10 % and 30 % attrition at months 6 and 24, respectively, our sample size of 240 will be powered to detect a 9 % difference between the two arms with regard to both optimal dose-taking adherence and undetectable viral load at both months 6 and 24.

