#### ART adherence

Adherence to one of the vitamins in the practice trials for those in the intervention arm, and to one antiretroviral (with the most complex regimen) for all participants once ART is initiated, will be measured electronically and continuously throughout the study using the Medication Event Monitoring System (MEMS) caps. MEMS caps house a microelectronic chip that records the date and time of each bottle-opening, enabling a precise, objective assessment of the timing of each dose and the patient’s pattern of pill-taking. Participants will be instructed to refill the bottle when removing the last remaining dose, to use the bottle provided for the monitored medication, and to remove only one dose at a time when the medication will be ingested. Participants do not always follow these instructions (e.g., removing multiple doses at once or “pocketing,” or opening the bottle without removing a dose), so we will assess this via self-report using a “past 2 weeks” time frame at each primary assessment and will adjust the number of prescribed does taken during this time period, which has been validated and shown to strengthen the relationship between adherence and viral load [17]. We will ask patients to notify the coordinator if their provider changes their ART regimen.

Data taken from the caps are downloaded into a software file that calculates summary scores that include percentages of prescribed doses taken (dose-taking adherence) and prescribed doses taken within a specified window of time (dose-timing adherence). For the analysis, we will examine both mean dose-taking adherence and proportion with ≥85 % dose-taking adherence as primary outcomes, as well as mean dose-timing adherence and proportion ≥85 % dose-timing adherence as secondary outcomes. We will also ask participants to self-report the number of doses missed in the last week and percentage of prescribed medications taken in the last month, which will be used as secondary outcomes.

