### Data analysis

The primary aim of the analysis is to determine whether the START intervention is superior to usual care in helping patients achieve optimal adherence and virologic suppression in both the short and long term. Dose-taking adherence and viral load are the primary outcomes. Continuous adherence will be assessed for normality and transformed if needed; viral load data will be log-transformed. Our primary analysis is based on an intent-to-treat approach, with secondary analyses involving study completers. Attrition weights will be used to account for dropouts, and all analyses will incorporate design effects from this weighting in the calculation of standard errors and tests of significance. Analyses will be conducted to compare groups at months 6 and 24 to assess short- and long-term effects.

In addition to simple between-group comparisons at each time interval (baseline and months 6, 12, 18, and 24), we will conduct analysis of the trajectory of outcomes. Longitudinal analyses will be performed, using mixed effects models to examine differences in trajectories of adherence and HIV viral load across the two groups, controlling for patient characteristics. Linear mixed effects models will be used for continuous outcomes, while nonlinear mixed effects models will be used for binary outcomes (e.g., took at least 85 % of prescribed doses, undetectable viral load). Along with a fixed linear term for time, a random subject-specific intercept will be incorporated, with the appropriate covariance structure of the repeated measures being determined during analysis. Covariates added to the models will include components of our conceptual IMB framework and intervention (e.g., HIV knowledge, adherence motivation, adherence self-efficacy), as well as correlated process variables (e.g., number of practice trials completed, total number of sessions attended). To adequately model longitudinal HIV viral load, which has a high proportion of values below the limit of detection, a Bernoulli/log-normal random effects mixture model with left censoring will be used [18, 19]. Analysis of covariance will be used to define an effect size estimate in the analysis of the primary outcomes and to provide baseline adjustment to improve statistical power.

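### If baseline is a response row, the linear time term in the supplementary viral-load trajectory models distorts how the arm difference develops; code time as categorical visit

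*Protocol article*

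**What the plan says.** The Data analysis section of the protocol article plans mixed models to "examine differences in trajectories of adherence and HIV viral load across the two groups". Their mean structure over time is given as "Along with a fixed linear term for time, a random subject-specific intercept will be incorporated", and what is left for later is the covariance: "with the appropriate covariance structure of the repeated measures being determined during analysis". No visit factor, spline or change-point is mentioned. A Bernoulli/log-normal mixture model is named for longitudinal viral load because of the detection limit, with no other time shape stated for it.

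These models are additional. The same section plans "Analyses will be conducted to compare groups at months 6 and 24 to assess short- and long-term effects", and introduces the trajectory analysis with "In addition to simple between-group comparisons at each time interval (baseline and months 6, 12, 18, and 24" (the list of visits ends there). ANCOVA is to supply effect sizes and baseline adjustment for the primary outcomes.

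Under Study sample, patients must not currently be on ART and must have "detectable HIV viral load at last test (within past 6 months" as the window for that test. Under ART adherence, electronic monitoring of treatment applies "to one antiretroviral (with the most complex regimen) for all participants once ART is initiated".

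**The concern.** Viral load is bound to change abruptly in this trial. At entry essentially nobody is undetectable in either arm, and there is no treatment effect yet. By month 6 patients have been on ART for half a year, and most of the fall has already happened. From then on the question is whether the arm difference holds, grows or fades.

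A line through baseline and the four later visits has to spread that early step over 24 months. The arm difference inherits the problem: it is zero at baseline and takes its value from month 6, but the model allows it only to start somewhere and move at a constant rate. At stake is the reading of durability. Study design states the time points as "Primary endpoints will be month 6 (short-term effect) and month 24 (to test durability of effect", and a trajectory model is a natural place to look for evidence that an effect lasts. As specified, it could show a stable effect as growing, or a fading one as stable.

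**Working it through.** The article gives no figure on this point to reproduce, so the check is of what the stated model does to known patterns.

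**Inputs from the article.** Visits at 0, 6, 12, 18 and 24 months; linear time; random intercept; 120 patients per arm (240 at 1:1); attrition 10% at month 6 and 30% at month 24; 45% undetectable expected in controls; a stated detectable difference of 9 points.

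**Assumptions.** An arm-by-time term is in the model (implied by the aim of comparing trajectories, not spelled out). Baseline is a response row (left open). The true arm difference is zero at baseline.

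**Method.** With complete data, the arm and arm-by-time estimates of a random-intercept model equal a least-squares line through the arm differences D(t). Mean time is 12. The sum of squares is 144 + 36 + 0 + 36 + 144 = 360. The slope is b = Σ(t − 12)D(t)/360, and the fitted difference is mean(D) + b(t − 12).

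1. *Sustained benefit*, D = 0, d, d, d, d. Mean = 0.8d. Slope = (−6 + 0 + 6 + 12)d/360 = d/30 per month.
2. *Waning benefit*, D = 0, d, 0.75d, 0.5d, 0.25d. Mean = 0.5d. Slope = (−6 + 0 + 3 + 3)d/360 = 0.

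| Pattern | Month 0 | 6 | 12 | 18 | 24 |
|---|---|---|---|---|---|
| Sustained, true | 0 | d | d | d | d |
| Sustained, fitted | 0.4d | 0.6d | 0.8d | 1.0d | 1.2d |
| Waning, true | 0 | d | 0.75d | 0.5d | 0.25d |
| Waning, fitted | 0.5d | 0.5d | 0.5d | 0.5d | 0.5d |

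The sustained benefit is 40% too small at month 6 and 20% too large at month 24.

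3. *Months 6 to 24 only.* A constant d is fitted as d at every visit with slope 0. Nothing is distorted.

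**Mixed-model simulation (log10 viral load).** Assumed means are 4.5 at baseline in both arms, then 2.5 (control) and 2.0 (START), so the true difference is −0.5 from month 6. Subject and residual SDs are 0.7, with 120 per arm, attrition rising from 10% to 30%, and 60 replicates per layout.

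| Layout and time coding | Month 6 | Month 24 |
|---|---|---|
| Baseline in, linear | −0.28 | −0.63 |
| Baseline in, categorical | −0.49 | −0.51 |
| Months 6–24, linear | −0.51 | −0.51 |
| Months 6–24, categorical | −0.49 | −0.49 |

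The first row is close to the 0.6 × −0.5 = −0.30 and 1.2 × −0.5 = −0.60 predicted above. The arm-by-time test rejected in 78% of runs with baseline in (Monte Carlo standard error √(0.78 × 0.22/60), about 5 points) and in 3% without it.

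**Undetectable yes/no.** Logistic fits to expected proportions, without random effects and with 0% at baseline, gave:

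- 45% against an assumed 65%: 12.1 points at month 6 and 22.4 at month 24, true value 20.
- 45% against 54% (the article's 9 points): 5.4 and 10.4 points, true value 9.

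**The case against.** The strongest reply is that the trial's main answers do not come from this model. The comparisons at months 6 and 24, and those at each visit, are planned directly and assume nothing about linearity. A reader might infer that the primary results are compromised, or that the trial cannot tell a lasting effect from a fading one. The article does not support that, because the visit-by-visit comparisons separate the two. This objection stands and limits the point to a supplementary analysis.

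Three further limits also stand.

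- It is tempting to extend the criticism to all outcomes. On-ART monitored adherence starts with ART and has no earlier value, so it has no baseline jump.
- If only months 6 to 24 are modelled, a constant benefit gives an arm-by-time slope of zero. That might look like a missed effect, but it is the correct answer: the arm term carries the benefit.
- Poor fit of the overall mean curve is not an error in the arm difference. With assumed means of 4.5 at baseline and 1.7 afterwards, the line gives 2.82 at month 6, about 1.1 log too high. Where both arms share that fall, the misfit cancels in the contrast.

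It can also be said that baseline handling is unstated and that a full analysis plan is promised before unmasking. That is fair as to baseline handling, and it makes the point conditional. It does not cover the shape of time, which the article specifies.

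**Conclusion.** The point holds for the viral-load trajectory models (log viral load and undetectable yes/no), on condition that the baseline visit is a response row. A sustained benefit is then shown as rising from 0.6d at month 6 to 1.2d at month 24, with a false 0.4d at baseline, and a benefit waning by equal steps to 0.25d is shown as a flat 0.5d. The multiples are exact for balanced data with a random intercept. Attrition, another covariance structure or the logit scale shifts them somewhat, as the simulation and the logistic fits show, but a line still cannot follow a step.

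Not every fading pattern is hidden. A benefit of 20, 10, 5, 0 points has mean 7 and slope (−120 + 30)/360 = −0.25 per month, so it is fitted as 8.5 at month 6 and 4 at month 24: falling, but far too low at first and too high at the end.

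The primary comparisons stand. The change is worth making because the model's output could be cited on durability.

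**What to change.** In the viral-load trajectory models, including both parts of the Bernoulli/log-normal mixture, replace the linear term with visit as a categorical factor (months 6, 12, 18, 24) plus an arm-by-visit interaction. Enter baseline log10 viral load, the last value before randomisation, as a covariate and not as a response row, in keeping with the baseline adjustment already planned through ANCOVA. Report the arm contrasts at months 6 and 24 from this model; the difference between them is a one-degree-of-freedom reading of durability. The same time coding can be used for adherence, for consistency.

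The cost is a change of wording before unmasking and a few degrees of freedom. Intercept, arm, three visit terms and three interactions make 8 mean parameters, against 4 for intercept, arm, time and arm-by-time. That is four more per model, or four more in each part of the mixture, with about 240 × 0.70 = 168 patients expected at month 24. No new data are needed.

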### Adherence interventions

#### Usual clinical care

Usual care procedures to enhance adherence at the clinics will continue to be implemented for all participants. Strategies for assessing adherence readiness at the study sites include educating the patient about the importance of adherence, evaluating patient commitment and motivation to adhere to treatment, and assessing whether barriers to adherence need to be addressed before initiating treatment (e.g., unstable housing, substance abuse). Once ART is initiated, routine inquiries about adherence occur at regular follow-up visits (once or twice in the first month of treatment, and then every 3–6 months). What varies across individual patients is the staff member who discusses these issues with the patient (e.g., nurse, physician, case manager) and the amount of time spent on these issues. Structured, systematic counseling protocols and practice trials are not part of usual care. We will measure adherence support received by patients as part of usual care in the participant surveys, as described below.

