##### Pretreatment training phase

This phase is composed of a series of up to four 1-week practice trials accompanied by adherence counseling and a dose regulation mechanism in which patients discontinue the practice trials and initiate ART once >85 % dose-taking adherence is achieved in a single practice trial, thus demonstrating adherence readiness. Using 85 % adherence to define readiness is consistent with what the literature indicates is needed for optimal treatment benefits with the new, more potent ART regimens [1–3]. With today’s common once-daily regimens, this threshold allows the patient to miss one dose over the course of the week and still meet the criteria for readiness. Early exercises and sessions will be focused on enhancing motivation and confidence to help prepare the patient for later skill-building exercises that may call for behavior change to overcome adherence barriers.

***Session 1*** Following an introduction and description of the ART regimen, the counselor will provide education about concepts such as viral load, drug resistance, and the importance of dose-timing to ensuring a constant adequate drug level. The importance of being ready to adhere well before starting treatment will be emphasized. Motivational interviewing (MI) techniques [16] will be used to help the patient develop or strengthen positive attitudes toward treatment and adherence, with the goal of improving adherence self-efficacy and motivation to adhere well. Exercises will be devoted to enhancing social support (reminders, transportation to clinic, provide reinforcement for successful adherence) provided by the patient’s social network. The practice trial will be introduced as an opportunity to experience what it is like to follow the prescribed ART regimen and to evaluate the patient’s readiness to start treatment. The practice trial regimen will mimic what the patient’s provider intends to prescribe. A 1-week supply of vitamins, with the electronic monitoring cap attached to one of the pill bottles, will be given to the patient to complete over the coming week.

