##### Maintenance training phase

The pre- and early-treatment phases help patients to be ready to adhere well at the beginning of treatment, but the skills needed to sustain adherence readiness over the long term may be quite different from those needed at initiation; hence the need for ongoing support. Maintenance modules will start at week 12 and thereafter at each routine clinic visit scheduled by the primary care provider as part of usual care, with the goal of helping patients sustain a high level of adherence over the course of treatment. Each module is composed of biweekly sessions and is dose-regulated such that patients who achieve >85 % dose-taking adherence during the prior month receive only one session while others receive sessions until >85 % adherence is achieved during the 2-week period preceding each successive session. For example, if the patient’s adherence from weeks 8 to 12 is 85 % or greater, then the patient will receive just the training session at week 12 and not return until the next routine clinic visit. However, if the patient’s adherence is <85 %, the patient will return for another session at week 14. The number of these biweekly sessions will be capped at three within each module. As with the pretreatment training, this dose regulation mechanism allows for varying the amount of training to the needs of the individual patient and for more efficient use of limited clinic resources for adherence support. The content of the maintenance training sessions will be similar to that during the early-treatment training phase, with continued emphasis on identification and resolution of adherence barriers, side effect management, and use of social support to help ensure commitment and motivation for long-term adherence.

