### Measures

Below are descriptions of the primary and secondary outcomes with regard to ART adherence, virologic suppression, immune function and HIV care retention (see Table 2). The survey assessment includes measures of potential mediators of intervention effects (e.g., components of the IMB model such as HIV knowledge, adherence motivation and self-efficacy, as well as depression and substance use), and potential moderators (e.g., demographics), but these are not described in detail here; however, we do describe below our survey measures of adherence support received from HIV providers as part of usual care. The survey will be facilitated using computer-assisted self-interview technology, which automatically stores survey responses; survey data files will be stored on password-protected, encrypted files.

**Table 2 Tab2:** Primary and secondary outcomes

Outcome measures	Outcomes
Primary outcomes	
HIV viral load (chart-abstracted HIV RNA)	Undetectable viral load (binary) (primary) Log change in viral load from baseline (continuous)
Dose-taking adherence (MEMS)	Took at least 85 % of prescribed doses (binary) (primary) Percentage of prescribed doses taken (continuous)
Secondary outcomes	
Dose-timing adherence (MEMS)	Percentage of prescribed doses taken in correct time window (±2 h for twice-daily regimens and ±3 h for once-daily regimens) (continuous) Took at least 85 % of prescribed doses on time (binary)
Dose-taking adherence (self-report)	Percentage of prescribed doses taken in past 7 days (continuous) Took at least 85 % of prescribed doses (binary) Visual analogue scale rating from 0 % to 100 % adherence over past 30 days
Dose interruptions (MEMS data)	Number of >48-h interruptions
Clinic attendance (chart abstract; self-report)	Number of attended and missed clinic appointments in past 6 months
CD4 count (chart-abstracted)	Change from baseline

*MEMS* Medication Event Monitoring System

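### The longitudinal mixed models adjust the arm comparison for practice-trial and session counts and for possible mediators, so their arm main effect is not the effect of START

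*Protocol article*

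**What the plan says.** All references are to the protocol article.

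- **Data analysis** adds longitudinal models to the simple comparisons at each visit, "using mixed effects models to examine differences in trajectories of adherence and HIV viral load across the two groups". They are linear for continuous outcomes and nonlinear for binary ones, so they cover both primary outcomes.
- The same paragraph continues: "Covariates added to the models will include components of our conceptual IMB framework and intervention", with HIV knowledge, motivation and self-efficacy as examples, and then "correlated process variables (e.g., number of practice trials completed, total number of sessions attended". This is worded as a commitment. Nothing limits these variables to a mediation analysis or to the START arm.
- **Measures** introduces the IMB scores as "measures of potential mediators of intervention effects".
- **Usual clinical care** states: "Structured, systematic counseling protocols and practice trials are not part of usual care".
- **Pretreatment training phase** states: "This phase is composed of a series of up to four 1-week practice trials". The series stops once the adherence threshold is met, and another trial follows if it is not.
- **Maintenance training phase** explains that "this dose regulation mechanism allows for varying the amount of training to the needs of the individual patient": one session per module for patients above the threshold, up to three for the others.
- **Data analysis** also declares an intent-to-treat primary analysis and a baseline-adjusted analysis of covariance for the effect size. It names no IMB or process covariates for the simple comparisons or for that analysis.

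**The concern.** A model that estimates the effect of a randomised intervention should condition only on what was fixed before randomisation. Two of the planned covariate groups break this rule or may break it.

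The trial and session counts are part of the treatment itself. They do not vary among controls, and among START patients they respond to the same behaviour that the outcome measures. IMB scores, if taken after START has begun, lie on the path through which START is meant to work.

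At stake is the arm effect that these models would report for adherence and viral suppression. An inert intervention could appear strongly beneficial or harmful, and a real effect could be hidden.

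**Working it through.** The plan gives no figure to reproduce here. The check reads the design rules and then illustrates them.

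**1. Range of the counts by month 6, from the intervention sections**

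| Count | Usual care | START |
|---|---|---|
| Practice trials | 0 | 1 to 4 |
| Pretreatment sessions (the first, plus one per trial) | 0 | 2 to 5 |
| Early-treatment sessions | 0 | 2 |
| Maintenance sessions (1 to 3 per module; 1 or 2 modules assumed by month 6) | 0 | 1 to 6 |
| Total sessions scheduled | 0 | 2+2+1 = 5 to 5+2+6 = 13 |

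**2. What the adjusted coefficient means.** Take least squares with arm and session count S, where S = 0 for every control. The slope c on S is then estimated from START patients alone, and

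arm coefficient = (START mean − control mean) − c × (mean S in START).

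The first term is the randomised comparison. The second moves it to S = 0, outside the scheduled range of 5 to 13. If poor adherers accumulate sessions, c is negative and the arm effect is inflated. If good adherers attend more of what is offered, c can be positive and the arm effect is pushed down.

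**3. Illustration, continuous adherence.** All inputs are assumptions except the stopping rules, the caps and 120 per arm. Each patient has a standard normal tendency u, and L = u + effect × arm. Trial k succeeds with probability logistic(0.3 + u + 0.2k), up to 4 trials. Sessions = 1 + trials + 2 + two modules of up to 3, each session ending its module with probability logistic(−0.2 + L). Adherence = 70 + 15L + normal noise (SD 12). Attendance is either full or has probability logistic(1 + e·u) per session. There were 400 runs. Cells show the mean arm coefficient in percentage points, with the share of runs with p < 0.05.

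| True effect | Attendance | Arm only | + trials | + sessions | + both |
|---|---|---|---|---|---|
| 0 | full | 0.0 (5%) | 12.4 (89%) | 45.3 (100%) | 46.1 (100%) |
| 0 | e = 1.5 | −0.2 (6%) | 12.1 (91%) | −23.6 (100%) | −11.3 (48%) |
| 0 | e = 3 | 0.0 (4%) | 12.2 (90%) | −19.5 (100%) | −10.8 (59%) |
| 4.95 | full | 4.9 (49%) | 17.0 (100%) | 48.6 (100%) | 49.6 (100%) |
| 4.95 | e = 1.5 | 5.0 (52%) | 17.5 (100%) | −18.8 (98%) | −6.1 (16%) |
| 4.95 | e = 3 | 5.0 (50%) | 17.3 (99%) | −14.9 (100%) | −6.3 (17%) |

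The formula in step 2 accounts for the sign. In row 1 mean S is 8.4, so c ≈ −45.3/8.4 = −5.4 points per session. In row 2 mean S is 5.3, so c ≈ (−0.2 + 23.6)/5.3 = +4.4.

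**4. Illustration, binary adherence, no true effect.** Logistic model, 108 per arm (120 × 0.9), true adherence drawn from Beta(3.2, 1.1), outcome at least 24 of 28 doses.

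| Model | Attendance | Log odds ratio for arm | Rejection |
|---|---|---|---|
| Arm only | – | 0.04 | 4.2% |
| + sessions | full | 8.21 | 100% |
| + sessions | flat 80% | 5.97 | 100% |
| + sessions | tracks adherence | 1.10 | 26% |
| + trials | full | 2.45 | 99.8% |
| + trials | tracks adherence | 2.41 | over 99% |

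**5. Arm-by-time term.** A null linear mixed model was run with 120 per arm, four visits, the same Beta distribution and dose rules, six assumed modules and non-informative dropout of 10% to 30% (200 runs). Adding both counts as fixed patient totals moved the arm main effect from −0.2 to +45.3 points (the match with step 3 is coincidence). The arm-by-time estimates with and without the counts were 0.073 and 0.076 points per visit, with rejection of 7.0% and 7.5%. This is expected, because a covariate that is constant within a patient says little about change within that patient.

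**6. IMB scores.** In a linear model without confounding between mediator and outcome, if a share m of the effect runs through the score, adjustment leaves (1 − m) of it: all at m = 0, half at m = 0.5, none at m = 1. The documents do not give m. Data analysis also does not say whether baseline or follow-up scores enter. Study design issues the assignment after the baseline survey. Study sample places the START baseline visit on the day of the last pretreatment session. Under the second reading even baseline scores follow two to five START sessions.

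**The case against.** The strongest reply concerns reach. The primary objective is tied to months 6 and 24, and Data analysis serves it with direct group comparisons and a baseline-adjusted analysis of covariance. The covariate sentence belongs to the additional longitudinal models. A reader might infer that the month 6 and 24 results are invalid too, but the document does not attach these covariates to them. This part of the reply stands.

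A second reply is that trajectory models are chiefly about the arm-by-time term, which step 5 leaves nearly unchanged. This stands for counts entered as fixed totals in a linear model. It does not rescue the arm main effect, and running counts or follow-up IMB scores could still disturb the slope.

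Third, a reader might infer that session adjustment always manufactures a benefit for START. Step 3 shows that the sign can reverse, because the covariate is sessions attended, not sessions offered. Likewise, complete loss of the effect through IMB adjustment follows only if mediation is assumed to be complete.

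Finally, the article promises a full analysis plan before unmasking. That would excuse silence, but here the covariates are already named, and a plan that follows the article inherits the problem.

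**Conclusion.** The concern holds for the longitudinal mixed models and should be fixed there.

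- **Counts.** The structural argument rests on the protocol alone: the counts are zero in one arm, driven by adherence in the other, and the adjusted arm main effect refers to a START patient the design does not schedule. In every scenario run, adjusting for either count or both biased that effect. The sizes depend on assumed adherence and attendance, and for sessions so does the sign.
- **IMB scores.** Follow-up scores would remove the mediated share, whose size is unknown. Baseline scores are acceptable only if measured before randomisation in both arms, which the article leaves contradictory.
- **Not shown to be affected.** The simple month 6 and 24 comparisons, the analysis of covariance, and the arm-by-time term when counts enter only as fixed totals.

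**What to change.** In Data analysis, state that every mixed model estimating the START effect uses only pre-randomisation covariates, for example site, prior ART history, CD4 stratum, pre-randomisation log viral load and demographics. Remove the practice-trial and session counts and any post-randomisation IMB score from these models. Place the IMB components in a separate mediation analysis labelled as such, and report the counts descriptively within the START arm. Reconcile Study design and Study sample on when the START baseline assessment takes place before any baseline IMB score is used as a covariate.

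The cost is a change of wording before unmasking. No data collection or sample size changes, and the mediation and dose questions are still addressed as secondary analyses.
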